**Quantitative measures**		
	Volume of users (GA^a^)	Proportion of users who return to the website (GA)
	Average time spent on the website (GA)	Acceptability of Intervention Measure questions (PS^b^; Figure 4)
	The average number of resources the users clicked on in different stages (GA)	—^c^
	Total number of times a resource was clicked within each stage (GA)	—
	User demographics (age, gender, location, language, and accessing the website for themselves or for a friend or family member; GA and PS)	—
**Qualitative measures**		
	Focus group interview guide assessing reach: Do you think people would use the website? Who do you think would use the website? (FG^d^)	Open-ended questions about acceptability; for example, “What did you find most helpful?” and “What were you expecting to find that was missing?” (PS; Figure 4)
	Focus group assessing who it would be useful in reaching: Who do you think would use this website the most? (People living with OUD, family, friends, SUD^e^ professionals?)	Focus group interview guide assessing safety, acceptability, usability, and further feedback on usefulness. Example questions are “What are your overall impressions or thoughts on the website?” and “Is there something on the website you particularly liked/disliked?” (FG)

^a^GA: Google Analytics.

^b^PS: pop-up survey.

^c^No additional information.

^d^FG: focus group.

^e^SUD: substance use disorder.

We will measure the volume of users who access the website and user demographics to characterize who we are reaching. We will measure the average time spent on the website, the average number of resources the users clicked on, and the total number of times each resource was clicked on. This will help determine whether users genuinely engage with the website and identify which stages and specific resources are most relevant to them. Google Analytics provides data on how many users visit the website, when they visited, how long they stayed on the website and on specific pages, and what resources they clicked on, along with users’ age, gender, location, and language preferences. Information on demographics, such as age and gender, and whether the users are visiting the website for themselves or for a friend or family member will also be asked in a pop-up survey that will appear when people leave the website (Figure 4).

**Figure 4 figure4:**
[figure not shown]
A pop-up survey that will be presented to users before they leave the website to collect demographic information and initial acceptability of the website. MOUD: medications for opioid use disorder.

To further assess acceptability, we will measure the proportion of users who return to the website along with using the Acceptability of Intervention Measure [41]. The pop-up survey will ask closed- and open-ended questions to assess acceptability and identify additional relevant resources. The closed-ended questions will use the 4 questions from the Acceptability of Intervention Measure [41]. The open-ended questions will ask about ways in which they found resources helpful, whether there are other topics or questions that they expected to obtain information on but did not find anything relevant, and whether there are any other resources they would like to share with the broader community. Google Analytics tracks the number (and proportion) of people who are returning users, which will be used as another measurement of acceptability.

Finally, we will compare users who come from Reddit versus those who come from Google by looking at the volume of users from each source and their characteristics. The aforementioned outcomes will be assessed to compare the effectiveness of social media versus search engines in disseminating resources such as the *MOUD Hub.*

For the website’s reach, we hypothesize that (1) users will most frequently click on links related to the precontemplation or contemplation phases of MOUD use, as opposed to links related to the preparation, action, and maintenance phases; (2) a substantial proportion of users (>25%) will be family members or friends of people who use opioids; (3) the volume of users referred through Google searches will be larger than that of users referred through Reddit; and (4) users referred through Reddit will spend more time on the website and click on a higher number of links than users referred through Google searches.

For acceptability, we hypothesize the following: (1) most users will find the resource useful and ratings will be significantly higher among acquaintances of people who use opioids than among people who use opioids themselves; (2) users with OUD will find the resource less useful; and (3) a large proportion of resources shared by users will lead to non–evidence-based information, including rehabilitation centers based on mandatory abstinence.

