#### Resources Provided and the Conceptual Framework of Access to Health

The *MOUD Hub* consists of a repository of evidence-based resources and links to web-based material to address barriers to MOUD treatment engagement and retention. To identify the challenges for which resources were needed, we conducted literature searches on MOUD barriers and facilitators and complemented these findings using insights from Reddit ([name], personal communication, 2024). Specifically, natural language processing methods were applied to Reddit textual data to understand the main struggles faced by people who use MOUD throughout their treatment ([name], personal communication, 2024). We used the results of the topic models that unveiled the main issues discussed in the r/Methadone and r/suboxone subreddits to guide sections of the *MOUD Hub* and help identify the resources needed. For example, the topic “Back to suboxone after relapse” guided the incorporation of links and materials in the *MOUD Hub*, elucidating the safest and best practices to resume suboxone treatment. The purpose of using this Reddit analysis to inform the website was to better cater to the needs of people seeking help on the web to address OUD, as their demographics and circumstances may differ from those not seeking help on the web.

Resources were obtained from verified sources that specialize in substance use, such as the Substance Abuse and Mental Health Services Administration, Centers for Disease Control and Prevention, and websites connected to the National Institute on Drug Abuse, as well as harm reduction organization websites, including the National Harm Reduction Coalition. Peer-reviewed papers were used as references for information to ensure that the content was based on evidence and supported by research. References are cited for every resource provided so that users can access information at its source.

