**Figure 3 figure3:**
[figure not shown]
An example of a check in box for the precontemplation stage. Each stage has a tailored check in with questions guided by the principles of motivational interviewing. Users will be able to answer the questions and download them to their personal devices.

Apps deemed useful, such as the Calm App, were added as resources. Although we recognize that some apps may not be tested through randomized controlled trials, we chose those that have been based on helpful practices, such as mindfulness and harm reduction [37]. The *MOUD Hub* informs users that these apps may not be evidence based but that they might find some of them useful when trying to use coping skills for their treatment.

The website explicitly includes disclaimers regarding the fact that it does not offer medical advice; the language used, which in some instances includes terms from other resources that may be considered stigmatizing and for which we have used quotation marks; and noting that the resources are compiled rather than created by us (Multimedia Appendix 2).

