### Dissemination

The dissemination of the *MOUD Hub* will follow web-based marketing strategies, which harness interest in a topic, as expressed by internet searches or membership to specific social media networks, to promote the resource and increase its uptake. We will use internet searches on Google and leverage Reddit subreddits or discussions focused on opioid use recovery, treatment, and overdose prevention.

For Google, we will advertise this website in response to specific searches using sets of words described by Patton et al [18]. For example, when someone googles “opioid+treatment,” they will see our advertisement. For Reddit, the website will be posted monthly in the subreddits of r/Methadone, r/suboxone, r/OpiatesRecovery, and r/Naloxone. We will advertise the *MOUD Hub* monthly and tailor the post to incorporate the month’s most discussed topic. The monthly frequency of the posts is driven by the subreddits’ constraints on the maximum number of research-related posts.

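### The return proportion is used as an acceptability measure and falls within the Reddit–Google comparison, but the study's own repeat advertising generates some returns, on a different footing in each source

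*Protocol article*

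**What the plan says.** In the protocol article, Outcomes and Measures, Table 2 places the proportion of returning users, taken from Google Analytics, in the acceptability column. The only other quantitative entry there is the Acceptability of Intervention Measure (AIM). The text after Figure 4 repeats the classification: "we will measure the proportion of users who return to the website along with using the Acceptability of Intervention Measure", and again "Google Analytics tracks the number (and proportion) of people who are returning users, which will be used as another measurement of acceptability". The same section then says that the outcomes already described will be used to compare social media with search engines. Statistical and Qualitative Analyses plans bivariate tests of outcomes between Reddit and Google users.

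Dissemination sets out two different advertising mechanisms. On Reddit, "the website will be posted monthly in the subreddits of r/Methadone, r/suboxone, r/OpiatesRecovery, and r/Naloxone", with each post adapted to the topic most discussed that month. On Google, "we will advertise this website in response to specific searches using sets of words". Results gives the collection period as January 2025 to January 2026.

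On the nature of the site, Resources Provided and the Conceptual Framework of Access to Health says that it "consists of a repository of evidence-based resources and links to web-based material". The Figure 3 caption says of the check-in box: "Users will be able to answer the questions and download them to their personal devices".

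Statistical and Qualitative Analyses lists the proportion of returning users with time on site and pages visited, that is, as a description of use. It gives an interpretation rule for the AIM (a mean between 4 and 5) and none for returns.

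**The concern.** A return visit speaks for acceptability only if the user came back because the site was found worth using. Two features of the design weaken that link.

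First, the study itself prompts returns. A Reddit member who visits early can meet a fresh study post in the same forum each month, and any click on it makes that person a returning user. Google has no corresponding schedule, and re-exposure depends on the user searching again. A difference in return proportion between sources would then mix a difference in prompting with any difference in how the site was received.

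Second, not returning is ambiguous. A visitor who follows a link to a treatment locator or helpline, or who saves the check-in answers, may be satisfied and have no reason to come back.

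At stake is mainly the source comparison, which Recruitment, Sample, and Participants says will help to choose the platform for future work. Neither that section's discussion of bias nor Limitations mentions re-prompting.

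**Working it through.** The plan states no expected return rate, threshold or sample size for this measure, so there is no figure to reproduce. The check is a reading of the design followed by an illustration on assumed inputs.

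**From the document:** monthly posts, the same four subreddits, one year of data, search-triggered Google advertising.

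**Assumed:** 12 posts; Reddit users first arrive in equal numbers at each post; each past visitor responds to any one later post with probability q, independently; a spontaneous return has probability a, independent of the prompts.

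**Step 1, exposure.** A user arriving at post m faces 12 − m later posts: 11 for the first post and 0 for the last. Eleven is a ceiling, reached only if every later post is seen.

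**Step 2, prompted return.** r = average over j = 0 to 11 of [1 − (1 − q)^j].

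**Step 3, observed return.** Total = 1 − (1 − a)(1 − r). With a = 10%:

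| q per later post | r | Total return | Added to 10% |
|---|---|---|---|
| 1% | 5.3% | 14.8% | 4.8 points |
| 2% | 10.3% | 19.3% | 9.3 points |
| 3% | 15.0% | 23.5% | 13.5 points |

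Unrounded, the last total is 23.46%, hence about 5 to 13 points.

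**Step 4, how far the inputs drive the answer.** The share of returners who came back only because of a prompt is (Total − a)/Total.
- a = 30%, q = 0.5%: r = 2.7%, Total = 31.9%, share = 6%.
- a = 5%, q = 10%: r = 40.2%, Total = 43.2%, share = 88%.

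For prompt-only returners to equal spontaneous ones, q would have to be about 1.0%, 2.2%, 5.4% or 11.0% when a is 5%, 10%, 20% or 30%. Nothing in the documents places the study within this range.

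**Step 5, the Google side.** Setting Google re-prompting to zero would leave Google at 10% in the Step 3 table, and the whole addition would appear as a Reddit excess. That zero is an assumption. If repeat searches brought back 10.3% of Google users while q on Reddit were 1%, Google would show 1 − 0.9 × 0.897 = 19.3% against 14.8% for Reddit. What the documents establish is unequal mechanisms, not a known direction.

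**The case against.** The strongest reply is that little depends on this measure. It has no threshold, the article calls it an additional measurement, and none of the seven hypotheses in Outcomes and Measures uses it. The AIM carries the only interpretation rule, and open-ended survey questions and focus groups also assess acceptability. All of this stands, so the overall acceptability conclusion is not in danger.

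It can also be said that reopening a site one has already seen shows some willingness to use it, especially when the post is tailored to a current topic. That stands too: prompted returns are not empty of approval, and the model in the working treats them as if they were.

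A third reply is that Google Analytics already records new or returning status and site of origin, and that attribution rules belong in a fuller document. That is fair for the technical detail. It does not cover what the article itself fixes: the label of acceptability, and the inclusion of the measure in a comparison where only one source has scheduled re-prompting.

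A reader might go further and infer that relapse drives returns. The documents do not support this. The recurrence-stage entry in Table 1 that points users back to harm reduction material is content read by someone already on the site, and Limitations says that the site cannot follow a user's progress. A past user who comes back during recurrence is using the site as intended. Link-out and download can only lower returns, so they show ambiguity and not inflation.

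**Conclusion.** The point holds in limited form. The return proportion partly reflects study-generated prompts as well as approval, by an amount likely to differ between Reddit and Google, and it is an ambiguous sign of acceptability on a site that links outwards. On assumed inputs (12 posts, even arrivals, 10% spontaneous return, 1% to 3% response per later post) the prompts add about 5 to 13 percentage points on Reddit. The true size is not fixed by the documents.

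Two stronger readings should not be drawn. One is that returns reflect reminders or relapse as much as approval: the illustrative share from prompts alone runs from 6% to 88%, depending wholly on the inputs. The other is that the bias will certainly favour Reddit: that needs Google re-prompting to be smaller, which is plausible but not stated. The change is worth making because it is nearly free and because the Reddit–Google comparison of returns cannot be interpreted without it.

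**What to change.** 1. Use tagged links in every Reddit post and Google advertisement from launch, so that visits starting from study advertising can be identified. Without tags, prompted and unprompted returns may not be separable afterwards.
2. In the source comparison, report returns that began from a study post or advertisement separately from unprompted returns, and compare Reddit with Google on the unprompted ones.
3. In Table 2 and the accompanying text, present the return proportion as a use-pattern measure, as Statistical and Qualitative Analyses already does. Rest the acceptability conclusion on the AIM and the qualitative data.
4. Add a sentence saying that a single visit is not by itself evidence of poor acceptability, since the site directs users to outside resources.

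The cost is minor link-tagging work and a few lines of text. The return figure used for comparison will be lower, and acceptability loses one supportive number. Some approval-driven returns that happen to start from a post will fall in the prompted group, which is why both groups should be shown.

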### Web-Based Information Seeking

Given the stigmatized nature of OUD, people have been shown to seek information about detoxification, rehabilitation, and treatment through web-based resources as this offers more anonymity and confidentiality. We recently published a paper showing significant positive associations between the number of Google searches specific to help seeking for OUD (eg, “heroin detox” and “treatment for opioid use”) and indicators reflecting OUD prevalence, including the number of people receiving MOUD, the number of emergency department visits related to opioid overdose, and the number of fatal opioid overdoses across states in the United States [18]. These findings suggest that leveraging Google search algorithms could be used to effectively reach people in need of help for OUD. Similarly, web forums are a source of support, trust, and knowledge building among people living with OUD, including in the context of treatment seeking and maintenance [19]. Specifically, Reddit, a publicly available social media platform, has several subforums (known as subreddits) available to discuss and share information on opioid recovery (eg, r/OpioidRecovery, r/OpiatesRecovery, r/Methadone, and r/suboxone). As of August 13, 2024, these 4 subreddits reached >130,000 users.

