There are no eligibility criteria for the study when assessing the website’s reach due to it being available for public access. We will be openly advertising it to people who make relevant Google searches or who are members of opioid-related subreddits. Similarly, there is no randomization, as all users can access the same website’s content. We will be able to identify whether participants came from Reddit or Google and treat them as 2 different samples. This will enable us to investigate differences in user volume and characteristics when accessing the website through Reddit or Google and to evaluate the most appropriate platform for dissemination for future-related interventions.

There is potential for bias, including misclassification, self-selection, and response bias. It will not be possible to know whether users are experiencing OUD or searching for information for a loved one, limiting our understanding of the representativity of the sample by OUD experience and leading to potential misclassification bias. However, we will be able to know whether users clicked on resources specific to friends or family and whether they responded to the “check-in” questions directed at people living with OUD. In addition, the pop-up survey asks whether users are accessing the website for themselves or a friend or family member. This will provide us with an additional measure for the proportion of users who are seeking help for themselves versus for a friend or family member.

Effectively, all people accessing the website will self-select based on need or curiosity, and we will miss information from people living with OUD who are not seeking help for OUD or are not compelled to access the *MOUD Hub* when exposed to it. The demographics data will allow us to assess to what extent our sample is representative of the general population and the population experiencing OUD and fatal overdoses in the United States in terms of geography, age, and gender. We will also be able to assess whether users are accessing the website from Google, Reddit, or other sources, potentially representing different communities. While response bias is possible in the context of our pop-up survey, participation will be voluntary and anonymous, and therefore, this will be minimized. However, there will undoubtedly be self-selection bias among the group answering the survey, likely representing those most engaged in improving access to reliable MOUD information*.*

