### Outcomes and Measures

To evaluate the safety and acceptability of the *MOUD Hub*, we will conduct pilot focus groups with 10 graduate students belonging to recovery groups or unions for people who use drugs. We will lead 2 focus groups to explore safety-related issues, along with gaining feedback on the acceptability, content, and any additional information that should be provided on the website. Safety concerns will focus on, but will not be limited to, information that may potentially be triggering or misleading and stigmatizing language.

A total of 4 additional focus groups will be conducted with other groups to gain more in-depth knowledge on the acceptability of the hub, user experience, and thoughts on its usefulness, following improvements from the pilot focus group. The topic guide in Multimedia Appendix 3 will be used.

To evaluate the reach and use patterns of the website, we will use Google Analytics to collect data on the number of users, their characteristics, and their interactions with the website [38,39]. The website will be launched in January 2025, and we will collect data for evaluation for a year and look at the data in 3-month increments. With this iterative approach, we can adjust the website in real time.

Our protocol’s outcomes and measures are shown in Table 2. We will first assess the dissemination reach of the website. The reach of an intervention is defined as “the absolute number, proportion, and representativeness of individuals who are willing to participate in a given initiative, intervention, or program, and reasons why or why not” [40].

**Table 2 table2:** Outline of the quantitative and qualitative measures that will inform the outcomes. Each measure is labeled with the information’s source.

Reach		Acceptability

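### User volume from Google and Reddit is to feed a comparison of dissemination effectiveness, although exposure differs by design and no measure counts people exposed

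*Protocol article*

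**What the plan says.** All references are to the Methods of the protocol article.

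- **Comparison.** Outcomes and Measures, after Figure 4: "we will compare users who come from Reddit versus those who come from Google by looking at the volume of users from each source", together with user characteristics. The next sentence states the inference: "The aforementioned outcomes will be assessed to compare the effectiveness of social media versus search engines in disseminating resources". Reach hypothesis 3 is that "the volume of users referred through Google searches will be larger than that of users referred through Reddit". Reach hypothesis 4 expects Reddit users to stay longer and click more links.
- **Use of the result.** Recruitment, Sample, and Participants: the difference between sources serves "to evaluate the most appropriate platform for dissemination for future-related interventions".
- **Exposure.** Dissemination, on Google: "we will advertise this website in response to specific searches using sets of words described by" an earlier paper. On Reddit: "the website will be posted monthly in the subreddits of r/Methadone, r/suboxone, r/OpiatesRecovery, and r/Naloxone". The section explains that subreddit limits on research posts set the monthly rhythm. It gives no budget, cap or serving share for the Google advertisement.
- **Definition of reach.** Outcomes and Measures adopts "the absolute number, proportion, and representativeness of individuals who are willing to participate in a given initiative".
- **Measures.** Table 2 lists five quantitative reach measures: user volume, average time on site, average resources clicked, total clicks per resource, and demographics. The only proportion it names as a measure is returning users, under acceptability and based on visitors.
- **Data source.** Data Collection and Management says that all data for the dissemination analysis come from Google Analytics and website traffic.

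**The concern.** The number of users a channel delivers is the product of how many times the resource was displayed and how often a display led to a visit. The plan observes the product only. If the two channels had equal exposure, volume would rank them by performance. They do not: one is triggered by searches without a stated limit, and the other is capped by forum rules.

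The plan still carries volume into a statement about the effectiveness of social media versus search engines, and into a judgement on the most suitable platform. A channel could look better simply because it was given more displays or more money, and a reader planning a later dissemination effort could not tell. The adopted definition of reach also asks for a proportion of individuals. Number is covered by volume, and representativeness by the planned demographic comparison with the general and OUD populations, but the proportion has no measure.

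**Working it through.** The plan states no exposure figure, sample size or power for this comparison, so there is no figure of its own to reproduce. The check is an identity plus an illustration.

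**Identity.** For channel *c*, users *U* = exposures *E* × access rate *a* (users per display). Hence

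U_Google / U_Reddit = (E_Google / E_Reddit) × (a_Google / a_Reddit).

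Only the left side is observed. The last factor is channel performance per display; the first is the amount of advertising.

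**Inputs.** From the Dissemination section: 4 subreddits, posted monthly, gives 4 × 12 = 48 posts in the data-collection year if each subreddit receives one post a month. Everything else is assumed, because the article gives no figures: 500 to 10,000 views per Reddit post, and 50 to 5,000 Google impressions per day over 365 days.

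**Case 1: identical access rates.** The rate cancels, so the volume ratio equals the exposure ratio:

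| Views per post (Reddit views per year) | 50 per day (18,250 per year) | 500 per day (182,500) | 5,000 per day (1,825,000) |
|---|---|---|---|
| 500 (24,000) | 0.76 | 7.6 | 76 |
| 2,000 (96,000) | 0.19 | 1.9 | 19 |
| 10,000 (480,000) | 0.04 | 0.38 | 3.8 |

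The Google-to-Reddit ratio runs from 0.04 to 76 with no difference in performance at all. The break-even number of Google impressions per day is 48 × views per post ÷ 365:

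- 500 views per post: 24,000 / 365 = 66
- 2,000 views per post: 96,000 / 365 = 263
- 10,000 views per post: 480,000 / 365 = 1,315

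**Case 2: Reddit performs better per display.** Assume access rates of 3% on Reddit and 1% on Google, 2,000 views per post and 5,000 impressions per day.

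- Reddit: 96,000 × 0.03 = 2,880 users
- Google: 1,825,000 × 0.01 = 18,250 users
- Ratio: 18,250 / 2,880 = 6.3 in favour of Google, the channel with the lower access rate

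**Can the data in the plan separate the factors?** No. The sources fixed in Data Collection and Management describe people who arrived at the site, and so does the pop-up survey. Recruitment, Sample, and Participants concedes that people who are exposed but do not visit are missed, but it does not connect this to the platform comparison. The Limitations section does not mention unequal exposure.

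**The case against.** The strongest reply is that attainable volume is a fair pragmatic question. The subreddit limit is a real property of Reddit as a channel, not a distortion introduced by the investigators, and a descriptive feasibility study may well ask how many users each channel delivers under its actual constraints. That stands: raw volume deserves to be reported as yield. It does not stand for the word effectiveness, because Google's yield also depends on a campaign size that the article does not state.

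A second reply is that an article leaves detail to a fuller document. Here, however, the article positively confines the dissemination data to site traffic, so this is a stated choice and not an omission.

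Several stronger readings are tempting but unsupported:

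- *Volume is the only reach measure or the only basis of comparison.* Table 2 has four other quantitative reach measures, and hypothesis 4 concerns time and clicks. Those are per-user quantities and need no exposure denominator.
- *The design guarantees that hypothesis 3 succeeds.* The table above includes ratios below 1. Volume depends on exposure; the direction is not fixed.
- *The result will choose the channel for the later randomized trial.* The text speaks of future interventions generally. The trial options in the Discussion are recruitment on both platforms, physical recruitment, or emergency departments.
- *The subreddit list in the Introduction must match the posting list.* The Introduction says "As of August 13, 2024, these 4 subreddits reached >130,000 users" of a list that includes r/OpioidRecovery and not r/Naloxone. But that list is offered as examples, and the figure is never used as a denominator.

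It is also fair to object that users divided by impressions is not the person-level proportion in the definition of reach. That limit is real and has to be stated with the rate.

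**Conclusion.** The point holds in a limited form. The volume comparison, and hypothesis 3 with it, cannot distinguish how well a channel turns exposure into visits from how much advertising it received. The proportion component of the adopted reach definition has no measure. The comparisons of time, clicks and characteristics are untouched.

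The structural conclusion rests only on the identity and on the article's own description of the two channels. Its size cannot be fixed from the article: the range of 0.04 to 76 and the 6.3-to-1 reversal depend on assumed views, impressions and access rates, and show only that the ambiguity can be large. This is an inexpensive improvement worth making before launch, since exposure records may not be recoverable afterwards. It does not undermine the study as a whole.

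**What to change.** 1. Amend Data Collection and Management and Table 2 so that Google ad impressions and spend, and Reddit post views where the platform reports them, are saved prospectively. Log staff time for the Reddit posts, so that cost per user can be formed for both channels.
2. For each channel, report users per 1,000 exposures and cost per user beside raw volume, with the confidence intervals the plan already promises for each outcome.
3. Describe raw volume, including the result for hypothesis 3, as yield under the campaign actually run, and do not interpret it alone as platform effectiveness. Where exposure counts cannot be obtained, remove the effectiveness wording for volume.
4. State the limit of the rate: impressions and post views count displays and not unique people, and they are not the same unit on the two platforms. Users per exposure is therefore only an approximate reach proportion, and the between-channel ratio needs the same caution.

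The cost is small: routine saving of platform reports where available, a simple time log, a few added rows in Table 2 and a few changed sentences. No additional data are collected from users.
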